**CONFIDENTIAL**

106464 (Malaria-049)  
Amendment 4 Final, 17 April 2008

|                                                  |                |                |                |                |                |                |                |                |                |                |                |                |                |                |                |                |
|--------------------------------------------------|----------------|----------------|----------------|----------------|----------------|----------------|----------------|----------------|----------------|----------------|----------------|----------------|----------------|----------------|----------------|----------------|
| Morbidity surveillance/record SAEs               | ● E | ● F | ● F | ● F | ● F | ● F | ● F | ● F | ● F | ● F | ● F | ● F | ● F | ● F | ● F | ● F |
| EFFICACY DATA COLLECTION                  |                |                |                |                |                |                |                |                |                |                |                |                |                |                |                |                |
| Record baseline covariates                       | ●              |                |                |                |                |                |                |                |                |                |                |                |                |                |                |                |
| Temperature (for ACD)                            |                |                |                |                |                |                |                | ●              | ●              | ●              | ●              | ●              | ●              | ● S | ●              | ●              |
| Blood slide for malaria parasites (for ACD)      |                |                |                |                |                |                |                | ● H | ● H | ● H | ●              | ● H | ●              | ● S | ● H | ● R |
| Rapid test for malaria parasites (for ACD)       |                |                |                |                |                |                |                | ● H | ● H | ● H | ● H | ● H | ● H | ● S | ● H | ● R |
| Parasite Genotyping (for ACD)                    |                |                |                |                |                |                |                | ● H | ● H | ● H | ●              | ● H | ●              | ● S | ● H | ● R |
| Passive Case Detection J              |                | ●              | ●              | ●              | ●              | ●              | ●              | ●              | ●              | ●              | ●              | ●              | ●              | ●              | ●              | ●              |
| SAFETY LABS                               |                |                |                |                |                |                |                |                |                |                |                |                |                |                |                |                |
| Complete blood count K                | ●              |                |                |                |                |                |                |                | ●              |                | ●              |                | ●              |                |                |                |
| Creatinine, ALT                                  | ●              |                |                |                |                |                |                |                | ●              |                | ●              |                | ●              |                |                |                |
| Hemoglobin                                |                |                |                |                |                |                |                |                |                |                |                |                |                |                |                | ● R |
| INVESTIGATIONAL ASSAYS                    |                |                |                |                |                |                |                |                |                |                |                |                |                |                |                |                |
| Antibodies to CS                                 | ●              |                |                |                |                |                |                |                | ●              |                | ●              |                | ●              |                |                | ● R |
| Antibodies to HBs                                | ●              |                |                |                |                |                |                |                | ●              |                |                |                | ●              |                |                |                |
| CS-specific T-cells (ICS assay)                  | ●              |                |                |                |                |                |                |                | ●              |                |                |                | ●              |                |                |                |
| T regulatory cells and function                  |                |                |                |                |                |                |                |                |                |                | ●              |                |                |                |                |                |
| Anti-blood stage humoral immunity                | ● Q |                |                |                |                |                |                |                | ● Q |                | ● Q |                | ● Q |                |                |                |
| CS-specific T-cells (ELISPOT assay) L | ●              |                |                |                |                |                |                |                | ●              |                | ●              |                | ●              |                |                |                |
| FINAL ANALYSIS                            |                |                |                |                |                |                |                |                |                |                | ● M |                |                |                |                |                |
| STUDY CONCLUSION                          |                |                |                |                |                |                |                |                |                |                |                |                | ●              |                |                |                |
| STUDY CONCLUSION                          |                |                |                |                |                |                |                |                |                |                |                |                |                |                |                | ●              |

for table notes, please refer overleaf...

Amended 23 October 2006  
Amended 20 November 2006  
**Amended 17 April 2008**

**CONFIDENTIAL**

106464 (Malaria-049)  
Amendment 4 Final, 17 April 2008

ACD: Active Case Detection PCD: Passive Case Detection ICS: Intracellular Cytokine Staining FW: Field Worker

A The survey will be postponed in the event of low case rates occurring during the first four months of surveillance

B These visits will occur in the double blind phase in the event that the survey at Clinic Visit 6 is postponed

C all antimalarial, systemic antibiotic and antipyretic medication to be recorded

D record administration of immunosuppressants or other immune-modifying drugs during this period (for corticosteroids this means prednisone or equivalent,  $\geq 0.5$  mg/kg/day. Inhaled or topical steroids are allowed and should not be recorded. ALSO all immunoglobulins and blood products should be recorded during this period. ALSO any antimalarials.

E SAEs related to study procedures will be collected

F Procedure for PCD will be followed

Amended 20 November 2006

H If documented fever

J Where the subject is febrile, blood test, rapid test, and parasite genotyping will be performed

K Includes analysis of hemoglobin, total white cell count and platelets.

L Done only in study participants enrolled by KEMRI, Kenya

M Final analysis will be delayed in the event of low case rates occurring during the first four months of surveillance

N Visit 39 to occur between 14 days post Dose 3 of vaccine and 20 days post Dose 3 of vaccine

O Carried out on Field Worker Visit Code # 55 ONLY

P Carried out on Field Worker Visit Code # 86 ONLY

Amended 23 October 2006

Q Samples from Tanzania will be analyzed at LSHTM and/or their collaborating laboratory, at GSK Biologicals and/or their collaborating laboratory, and in Tanzania. Samples from Kenya will be analyzed at LSHTM and/or collaborating laboratory, at GSK Biologicals and/or collaborating laboratory, and in Kenya

Amended 20 November 2006

● is used to indicate a study procedure that requires documentation in the individual CRF and ○ is used to indicate a study procedure that does not require documentation in the individual CRF. \*SAEs that are related to study participation or are related to a concurrent medication will be collected and recorded from the time the subject consents to participate in the study until they are discharged.

*† Clinic Visit 7 and Clinic Visit 8 can take place on the same day. For subjects who do not present at Clinic Visit 7, an interval of 14 to 17 months post Clinic Visit 2 to Clinic Visit 8 is acceptable. Subjects will be reconsented for the participation in the surveillance during the extension of the study.*

*‡ The timing of visit 9 will be in October 2008 in Kilifi, and in September 2008 in Korogwe, in order to finish follow up at the same calendar month at each site. This will mean a variable number of months after vaccination by individual children, as indicated in the table.*

*R Blood will not be drawn for hemoglobin or serology or parasite slide in the absence of fever from subjects who present for Clinic Visit 9 less than or equal to 14 days after Clinic Visit 7. Note that if the subject is febrile a rapid test and a parasite slide and genotyping specimens will be taken even if occurring in this period.*

*S If Clinic Visit 8 is more than 7 days after Clinic Visit 7 or if Clinic Visit 7 was not done.*

Amended 17 April 2008

It is the investigator's responsibility to ensure that the intervals between visits/contacts are strictly followed. These intervals determine each subject's evaluability in the according to protocol analyses (see Sections 4.3 to 4.6 and 10.7 for details of criteria for evaluability and cohorts to be analyzed). The intervals are tabulated in Table 4.

**Table 4 Intervals between study visits**

| Interval                                | Length of interval                                                                                              |
|-----------------------------------------|-----------------------------------------------------------------------------------------------------------------|
| Clinic Visit 1 → Clinic Visit 2         | 0 to 60 days                                                                                                    |
| Clinic Visit 2 → Clinic Visit 3         | 21 to 35 days                                                                                                   |
| Clinic Visit 3 → Clinic Visit 4         | 21 to 35 days                                                                                                   |
| Clinic Visit 4 → Clinic Visit 5         | 21 to 42 days                                                                                                   |
| Clinic Visit 5 → Clinic Visit 7         | 12 months $\pm$ 30 days                                                                                         |
| Clinic Visit 7 → Clinic Visit 8* | 0 to 3 months                                                                                            |
| Clinic Visit 9                   | Korogwe: September 2008 <math>\pm</math> 14 days
Kilifi: October 2008 <math>\pm</math> 14 days |

\* Clinic Visit 7 and Clinic Visit 8 can take place on the same day. For subjects who do not present at Clinic Visit 7, an interval of 14 to 17 months post Clinic Visit 2 to Clinic Visit 8 is acceptable.

*Amended 17 April 2008*

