- Two cross sectional surveys for efficacy will be performed at 4½ and 12 months post Dose 3 to determine parasite prevalence, parasite density and hemoglobin, *and under a separate consent, a third cross-sectional survey for efficacy will be performed in October 2008 in Kilifi and September 2008 in Korogwe to determine parasite prevalence, parasite density and hemoglobin.*  
*Amended 17 April 2008*
- In the event that malaria rates are lower in the year of the study the cross sectional survey, unblinding and analysis scheduled at 4½ months post Dose 3 will be delayed until approximately 245 children have experienced an episode.
- Anti-CS antibody titers will be determined at baseline, 1, 4½ and 12 month post Dose 3 *and under a separate consent, at a cross-sectional survey occurring in October 2008 in Kilifi and September 2008 in Korogwe* in all study participants.  
*Amended 17 April 2008*
- Anti-HBs antibody titers will be determined at baseline, 1 and 12 months post Dose 3 in all study participants.
- CS-specific IFN-γ ELISPOT responses will be evaluated at baseline, 1 and 12 months post Dose 3 in study participants at KEMRI, Kenya.
- Regulatory T-cell immune response will be determined at 4½ months post Dose 3 in all study participants.
- Anti-malaria blood stage humoral immunity will be determined at baseline, 1 and 12 months post Dose 3 in all study participants.
- Timing of final analysis is projected for 4½ months post Dose 3. The study will continue in a single-blind manner and be reported as an annex at the end of the study.
- The final analysis is projected to occur after the completion of 4 months of surveillance, at which time it is assumed that 36% of children in the control group will have been affected by a malaria episode. Assuming a true vaccine efficacy of 30%, 400 evaluable subjects per group will have 90% power to detect a difference between the groups using a two sided Fischer exact test with alpha level of 5%.
- The vaccine research teams will ensure that insecticide treated bed net use is optimized in the study population.
- Data collection: conventional Case Report Form (CRF).

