**Clinic Visit 4: Vaccination 3**  
Day 60

---

- Check study identification card of vaccinee.
- Carry out physical examination.
- Check contraindications to vaccination.
- Check elimination criteria.
- Record unsolicited adverse events experienced by the vaccinee since the last visit.
- Record pre-vaccination body temperature.
- Administer the third dose of RTS,S/AS01E or Rabies Vaccine intramuscularly in the left deltoid.

Each child will be assessed for at least 60 minutes after vaccination to evaluate and treat any acute adverse events.

- Record any post-vaccination solicited symptoms.
- Record any post-vaccination unsolicited adverse events.
- Record any post-vaccination SAEs.
- Record concomitant medication.

---

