**Clinic Visit 5: Cross-sectional visit for ACD**  
Day 90

---

- Check study identification card of vaccinee.
- Carry out physical examination.
- Record SAEs experienced by the vaccinee since the last visit.
- Record unsolicited adverse events experienced by the vaccinee since the last visit.
- Check elimination criteria.
- Record concomitant medication.
- Record axillary temperature of subject.
- Blood sample to collect 5 mL blood for analysis of:
  - hematology (complete blood count).
  - biochemistry (creatinine and ALT).
  - serology (antibodies to CS, HBs, anti-blood-stage humoral immunity).

- CMI:  
CS-specific T-cells (ICS);  
*At KEMRI, Kenya only: CS-specific T-cells (ELISPOT).*
- *In addition, blood will be drawn from all subjects for:*
  - Rapid test for malaria parasites (only if subject is febrile).
  - Blood slide for malaria parasites.
  - Blood test for malaria parasite genotyping.
  - Complete Blood Count.

Amended 20 November 2006

---

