**Clinic Visit 7: Final study visit**  
Month 14

---

- Check study identification card of vaccinee.
- Carry out physical examination, measure body weight.
- Record SAEs experienced by the vaccinee since the last visit.
- Check elimination criteria.
- Record bednet usage.
- Record concomitant medication.
- Record axillary temperature of subject.
- Blood sample to collect 5.0 mL blood for analysis of:

- hematology (complete blood count);
- biochemistry (creatinine and ALT);
- serology (antibodies to CS, HBs, anti-blood-stage humoral immunity);
- CMI
  - CS-specific T-cells (ICS);
  - At KEMRI, Kenya only:* CS-specific T-cells (ELISPOT).
- *In addition, blood will be drawn from all subjects for:*
  - Rapid test for malaria parasites (only if subject is febrile);
  - Blood slide for malaria parasites;
  - Blood test for malaria parasite genotyping;

Amended 23 October 2006.

---

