#### **Immunogenicity**

- Anti-CS antibody titers at 12 months post Dose 3 (Month 14) *and in October 2008 in Kilifi and in September 2008 in Korogwe.*

*Amended 17 April 2008*

- Anti-HBs antibody titers at 12 months post Dose 3.
- Frequency of CD4+ and CD8+ CS-specific T-cells expressing at least two of the following: IL-2, CD40L, TNF- $\alpha$  and IFN- $\gamma$  prior to vaccination and 12 months post Dose 3.

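### Table 4 centres Clinic Visit 7 about one month later than the Month 14 schedule, so its ATP window can exclude on-time 12-month assessments

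*Protocol*

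**What the plan says.** Section 5.14 gives the nominal times. "Clinic Visit 4: Vaccination 3" is Day 60, "Clinic Visit 5: Cross-sectional visit for ACD" is Day 90 (Month 3 in Table 3), and "Clinic Visit 7: Final study visit" is Month 14.

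The 12-month assessments are counted from Dose 3. Section 3 states: "Two cross sectional surveys for efficacy will be performed at 4½ and 12 months post Dose 3". Section 10.3 lists "Anti-CS antibody titers at 12 months post Dose 3 (Month 14", which makes Month 14 and 12 months after Dose 3 the same time point. Anti-HBs, T-cell frequency, parasite prevalence and density, and hemoglobin are also set at 12 months post Dose 3.

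Table 4 allows 21 to 42 days between Clinic Visits 4 and 5. For "Clinic Visit 5 → Clinic Visit 7" it gives "12 months $\pm$ 30 days". The text introducing the table tells investigators to keep strictly to the intervals and adds: "These intervals determine each subject's evaluability in the according to protocol analyses".

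**The concern.** If Clinic Visit 5 is at Month 3 and Clinic Visit 7 at Month 14, the interval between them is 11 months, not 12. The figure in Table 4 matches the distance from Dose 3 (Clinic Visit 4) to Clinic Visit 7, but the row starts one visit later.

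The row is a criterion for ATP evaluability, so the slip does more than confuse scheduling. A site that aims at 12 months after Dose 3 can generate window violations by doing what the endpoint section asks. A site that aims at the Table 4 target collects its 12-month blood samples and survey slides at about 13 months. The annex immunogenicity analysis takes the ATP cohort as primary (Section 10.11.3), so the cohort and the timing of its data would depend on which of the two statements was followed.

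**Working it through.** **Inputs** (all from the protocol): Dose 3 at Day 60; Clinic Visit 5 at Day 90, permitted 21 to 42 days after Dose 3; Clinic Visit 7 at Month 14 = 12 months after Dose 3; Table 4 interval from Clinic Visit 5 to Clinic Visit 7 of 12 months ± 30 days. A year is taken as 365 days.

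**1. Window as written.** 365 − 30 = 335 and 365 + 30 = 395, so 335 to 395 days from Clinic Visit 5.

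**2. Interval implied by the schedule.**
- In months: 14 − 3 = 11.
- In days: Clinic Visit 7 at Day 60 + 365 = 425, and 425 − 90 = 335.
- By the weekly visit numbers in Table 3: Clinic Visit 5 is ACD visit 3 and Clinic Visit 7 is ACD visit 51, so 48 weeks × 7 = 336 days.

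The 12-month figure is not reproduced. The nominal child, at 335 days, lies on the lower limit. There is no tolerance for a Clinic Visit 7 one day early or a Clinic Visit 5 one day late.

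**3. A child seen exactly 365 days after Dose 3.** Let x be the days from Dose 3 to Clinic Visit 5. The interval to Clinic Visit 7 is 365 − x, which runs from 365 − 42 = 323 to 365 − 21 = 344. The child is outside when 365 − x < 335, that is x > 30. Days 31 to 42 are 12 of the 22 permitted values.

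**4. The Table 4 window expressed in days after Dose 3** (x + 335 to x + 395, centre x + 365):

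| Clinic Visit 5, days after Dose 3 | Window for Clinic Visit 7 | Centre |
|---|---|---|
| 21 | 356 to 416 | 386 |
| 30 | 365 to 425 | 395 |
| 42 | 377 to 437 | 407 |

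The nominal centre of 395 days is about 13 months. The latest acceptable visit, 437 days, is about 14.4 months.

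**5. Excluded share among children seen on day 365.** It equals the share whose Clinic Visit 5 fell after day 30. It is 0% if all were at or before day 30 and 100% if all were later. It is 12/22 = 55% only if the dates are assumed to be spread evenly over days 21 to 42.

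**6. Sensitivity to the calendar convention.** With a 365.25-day year or 30-day months, the dividing line stays between day 30 and day 31.

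**7. The same check after correction.**
- 12 months ± 30 days from Clinic Visit 4 gives 335 to 395 days after Dose 3. Day 365 is central whatever the Clinic Visit 5 date.
- 11 months ± 30 days from Clinic Visit 5 gives about 305 to 365 days. The on-time intervals of 323 to 344 days all fall inside.

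**The case against.** Several limits are fair, and they stand.

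- **The schedule is not excluded outright.** The exactly nominal child is inside the window, on its edge. Any Clinic Visit 7 from day 377 to day 416 after Dose 3 is acceptable whatever the Clinic Visit 5 date, so a visit up to 12 days late removes the problem.
- **Dose 3 is not the origin of every 12-month endpoint.** The case-based endpoints in Section 10.3 run for 12 months from 14 days after Dose 3. Read literally, they end on day 14 + 365 = 379. A visit on that day is 379 − 42 = 337 to 379 − 21 = 358 days from Clinic Visit 5, always inside the window. Their cases come from ACD and PCD, and time at risk follows Section 10.9.4, so they do not depend on attendance at Clinic Visit 7.
- **There is a back-up.** Section 10.11.1 analyses efficacy on both the ATP and Total cohorts. Section 10.11.3 adds a Total Vaccinated Cohort analysis of immunogenicity if more than 5% of enrolled subjects are excluded from the ATP cohort.
- **The exclusion mechanism is only partly described.** Section 10.7 refers to compliance with protocol procedures and names no visit windows. Whether a violation at Clinic Visit 7 removes a child from the whole ATP cohort or from that time point may be settled in the Report and Analysis Plan, which is not at hand.

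None of this reconciles the row with the schedule. Table 4's own provisions for Clinic Visit 8 also point to Month 14: it may take place 0 to 3 months after Clinic Visit 7 or, if that visit was missed, 14 to 17 months after Clinic Visit 2. These match only if Clinic Visit 7 is at Month 14.

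**Conclusion.** The Table 4 row is wrong as written. It is one month longer than the interval between the visits it names, and it centres the 12-month window on about 13 months after Dose 3. It can reject a visit on the exact target day and accept one as late as day 437.

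The consequence is confined to the tertiary, annex-stage ATP analyses of the point-in-time 12-month assessments: anti-CS, anti-HBs, T-cells, parasite prevalence and density, and hemoglobin. The primary and secondary analyses use data up to Clinic Visit 6 (Section 10.10) and are unaffected.

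A reader might infer that about half of the on-time children will be lost, or that the 12-month efficacy result against clinical malaria is compromised. The documents support neither. The 55% figure needs an even spread of Clinic Visit 5 dates that the protocol does not state; the supportable range is 0% to 100%, and it applies only to children seen exactly on day 365. The clinical malaria endpoints have a different starting point and do not rest on this visit. The finding also assumes that the link in Section 5.13 between intervals and ATP evaluability is applied as stated.

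**What to change.** Reconcile the Table 4 row with Month 14 = 12 months after Dose 3, in one of two ways:

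- Replace the row with Clinic Visit 4 (Dose 3) to Clinic Visit 7, 12 months ± 30 days. This uses the reference point of the point-in-time 12-month assessments and does not depend on when Clinic Visit 5 took place.
- Keep Clinic Visit 5 as the starting point and state 11 months ± 30 days.

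Then apply the corrected window when judging ATP evaluability at Clinic Visit 7. The change is one table row. It needs no new data and leaves the endpoints and the sample size unchanged. Section 1.6.4 expects children to complete 12 months of surveillance between June and October 2008, so a correction alongside the amendment of 17 April 2008, which already revised Table 4, would precede those visits.
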